### 1.5.2 Secondary

Secondary immunogenicity and safety end-point information will be collected on all participants on the following:

- cellular responses
  - CD8/CD4+ T cell mean IFN $\gamma$  Spot Forming Units (SFU) per million cells across the peptide pools at weeks 26 and 28
  - CD8/CD4+ T cell mean Spot Forming Units (SFU) per million cells across the peptide pools at any week following the first immunisation including weeks 48 and 72
  - mean proportion of CD4/CD8+ T cells producing IL-2 and/or IFN- $\gamma$  following ex-vivo stimulation with HIV-1 peptide pools at weeks 26 and 28, 48 and 72
  - number of different epitopes that can be characterised
- antibody responses
  - precise assays to be determined at a later stage, but prior to unblinding of laboratory personnel
- all grade 1 and 2 adverse events
- all events including those considered unrelated

## 2 Schedule of Visits

### 2.1 Recruitment

Healthy volunteers will be recruited through the ANRS network of volunteers or through advertising in hospitals, colleges, newspapers and magazines and given a telephone number to contact. They will be provided with further information about the study, and asked to complete a short interview (by telephone or in person) to assess their suitability. At this point they will be allocated a number from the screening register. They will be given or sent an

information sheet (appendix 1) about the trial. The information to be provided and collected will be defined in the trial specific operating procedures and proformas.

If they are still interested and willing to participate, they will be invited to attend for screening.

## **2.2 Screening**

At this visit, which must take place within 42 days of the enrolment visit, the trial will be discussed in detail, and a more detailed check of eligibility conducted using a case record form to standardise this procedure. Any questions about the study will be answered. If volunteers are still willing and interested they will be asked to sign part 1 of the informed consent form (appendix 2).

To ensure informed consent, subjects will go through the following processes in detail with a member of the study team

- 1) Pre-HIV test counselling
- 2) Safe sex counselling
- 3) That it is unknown whether or not the study vaccines will protect against HIV infection
- 4) That following immunisation they may develop antibodies that will produce a positive reaction in a routine HIV test, but that provisions have been made to distinguish between a post vaccination response and HIV infection during and after the trial
- 5) The level of care that will be made available to them should they be found to be HIV infected at any time during their participation in the study, including the screening period.
- 6) That they, or their partner should continue to use a reliable form of contraception for 14 days prior to the immunisation period and for 4 months afterwards
- 7) That they should continue to use condoms with sexual partners whose HIV status is not known
- 8) That they may be subject to social risk if they develop HIV antibodies, or by revealing their participation in the study

After informed consent has been collected, assessments and procedures will be undertaken according to the schedule 2.6, including a physical examination and collection of specimens for laboratory investigations. Details of these are given in sections 3 and 4. The investigator will enter the data collected onto the case record form and on completion this will be sent promptly to the MRC CTU/INSERM for entry onto the trial database.

French volunteers should be registered in the French Health ministry computerised file by the investigators with a suspension duration of four months from the end of the study.

## **2.3 Enrolment and Trial Entry**

An enrolment list will be prepared by the CTU.

The results of the screening investigations will be reviewed and volunteers who are still eligible and willing will be asked to complete part 2 of the informed consent. This will include asking for consent to undertake long-term follow-up by direct contact. They will be strongly advised to inform their current general practitioner of their participation but this will not be a pre-requisite to enrolment. Assessments and procedures will be undertaken according to the schedules in 2.6, and data entered on the case record form.

Participants will be enrolled by completing the appropriate case report form and contacting the MRC CTU (EuroVacc centres) or INSERM U593 CTU (ANRS centres), with the participant present. Eligibility will be checked, the trial number confirmed and regimen allocated.

**The enrolment number is:****EuroVacc centres - [contact] [contact]****ANRS centres - [contact] [contact]**

Trial product will be dispensed as outlined in 1.4.3.

**2.3.1 Immunisations****Weeks 0, 4 and 8**

Two 2ml immunisations will be given at 0, 4 and to half the participants at 8 weeks, one into each vastus lateralis muscle in order to deliver 4ml total of the DNA C at each timepoint according to published guidelines [27].

**Weeks 20 and 24**

At weeks 20 and 24 or week 24 alone, a single immunisation will be administered into the deltoid muscle of the non-dominant arm.

During the procedure, regardless of muscle, the overlying skin will be stretched flat prior to insertion of the needle. To ensure that the needle reaches the muscle, and that product does not seep into the surrounding subcutaneous tissues, a decision about the needle length required will be made individually for each participant, based on published recommendations [27,28]. Ten minutes after immunisation, the site will be inspected and any local reactions recorded on the case record form. Following the NYVAC immunisation inspection, a plaster will be placed over the site.

The immunisations will occur in an outpatient setting, and participants will be closely observed for one hour after each immunisation, at which point vital signs (pulse, blood pressure and respiratory rate) will be recorded on the case record form, as will any local or systemic reaction.

The plasters, needles and syringes used for all immunisations will be autoclaved or placed in hypochlorite solution at the end of the clinical session.

**2.3.2 Follow-up in the days following immunisation**

A diary card will be given, with instructions and a full verbal explanation, for participants to record local and systemic adverse events for at least 7 days following immunisation, as well as medication taken.

Participants will be observed on the day of immunisation as above. Contact will be maintained by the clinical team, using a method chosen by the participant, as indicated by the evolution of adverse events, up to resolution of solicited local and systemic events. Additional visits may be recommended at the discretion of the clinical and principal investigators, if clinically indicated or in order to clarify observations.

**2.4 Follow-up visits**

Assessments and procedures will be performed according to schedules in 2.6.

**2.5 Final visit**

Assessments will be undertaken according to schedules in 2.6.

**2.5.1 Reimbursement**

Participants will be reimbursed for their travel expenses and any inconvenience caused according to site specific procedures, and this will be made clear to them in the information sheet. During the study participants will receive latex condoms free of charge. If any medication is required as a result of the study, this will also be provided free of charge.

**2.5.2 In the event of discontinuation**

It is possible that a participant may develop a condition, which regardless of the relationship to study product, may cause the Investigator to discontinue them from further immunisations. Follow-up should carry on whenever possible up to the time of the final visit, but at least until resolution or stabilisation of the condition. The date that the participant is discontinued from further immunisations and the reason will be recorded in the case record form.

## 2.6 EV03 Study schedule

| Visit Number                           | 1   | 2 | 3         | 4         | 5         | 6         | 7         | 8          | 9          | 10         | 11         | 12         | 13         | 14        | 15         |
|----------------------------------------|-----|---|-----------|-----------|-----------|-----------|-----------|------------|------------|------------|------------|------------|------------|-----------|------------|
| Time in wk (+/-wk or d)                | ≤-6 | 0 | 1 (+/-1d) | 4 (+/-3d) | 5 (+/-3d) | 8 (+/-3d) | 9 (+/-3d) | 12 (+/-3d) | 20 (+/-1w) | 22 (+/-1w) | 24 (+/-1w) | 26 (+/-1w) | 28 (+/-1w) | 48(+/-2w) | 72 (+/-3w) |
| Immunisation group 1                   |     | X |           | X         |           | X         |           |            |            | No visit   | X          |            |            |           |            |
| Immunisation group 2                   |     | X |           | X         |           |           | No visit  |            | X          |            | X          |            |            |           |            |
| Eligibility                            | X   | X |           |           |           |           |           |            |            |            |            |            |            |           |            |
| History & exam a            | X   | X |           |           |           |           |           |            |            |            |            |            |            | X         |            |
| STI screen b,c              | X   |   |           |           |           |           |           |            |            |            |            |            |            |           |            |
| HIV risk screen                        | X   |   |           |           |           |           |           |            | X          |            |            |            |            |           |            |
| HIV Ab test c               | X   |   |           |           |           |           |           |            | (X)        |            |            |            | X          |           |            |
| Safe sex counselling                   | X   |   |           |           |           |           |           |            |            |            |            |            |            |           |            |
| Adverse event assessment               |     | X | X         | X         | X         | X         | X         | X          | X          | X          | X          | X          | X          | X         |            |
| Haematology                            | X   |   | X         | (X)       | X         | (X)       | X         | (X)        | X          | X          | (X)        | X          |            | X         |            |
| Chem pathology                         | X   |   | X         | (X)       | X         | (X)       | X         | (X)        | X          | X          | (X)        | X          |            | X         |            |
| CD4 no & % & immnuoglob ns  | X   |   |           |           |           |           |           |            |            |            |            |            | X          |           |            |
| DNA/ANA antibodies                     | X   |   |           |           |           |           |           | X          |            |            |            |            | X          |           |            |
| Urinalysis                             | X   |   | X         | (X)       | X         | (X)       | X         |            | X          | X          | (X)        | X          | X          | X         |            |
| Pregnancy test, if female c |     | X |           | X         |           | Group 1   |           |            | Group 2    |            | X          |            |            | X         |            |
| Cell storage for HLA d      |     |   |           | X         |           |           |           |            |            |            |            |            |            |           |            |
| Sera storage d              |     | X |           |           |           | X         |           | Group 1    | Group 2    |            |            | X          | X          | X         |            |
| ELISPOT responses                      |     | X |           | X         |           | X         |           | Group 1    | Group 2    |            | X          | X          | X          | X         | X          |
| Flow cytometry                         |     | X |           |           |           |           |           |            |            |            |            | X          | X          | X         | X          |
| Cell storage                           |     | X |           | X         |           | X         |           | Group 1    | Group 2    |            | X          | X          | X          | X         | X          |
| Diary card e                |     | ↔ |           | ↔         |           | ↔         |           | ↔          |            | ↔          |            | ↔          |            |           |            |

aincluding weight in kg, height in cm and arm & thigh circumference in cm

bincluding serology for syphilis, hepatitis B and C at screening. Genital swabs or urine for Neisseria gonorrhoea, chlamydia trachomatis and trichomonas vaginalis will be collected if indicated according to clinical standardised operating procedures (SOPs).

c additional HIV/STI and pregnancy tests will be performed if indicated by a change in risk status or menstrual history respectively

dHLA genotyping will be performed for evaluation of epitopic responses in responders; serological assays to be determined at a later stage, but prior to unblinding of laboratory personnel

ediary card will be completed for at least 1 week following immunisation

fCD4 number and % only at this visit

(x) means that a specimen will be collected only if indicated on history

### **3 Procedures**

#### **3.1 Blood and urine collection**

Blood will be collected using a sterile needle, usually from the ante-cubital fossa, according to the schedule and transported to the appropriate laboratories. Urine will be collected into a sterile container as indicated on the schedule and either transported to the appropriate laboratory or tested by a member of the clinical team according to trial specific standardised operating procedures.

#### **3.2 Clinical history and examination**

A past medical history will be collected using the screening proforma at the screening visit, including details of any previous reaction to vaccination, history of epileptic fit, exposure to vaccinia, and contraceptive practices. The general examination will include weight (kg), height (cm) and arm and thigh circumference (see 4.1.1), blood pressure, inspection of the skin to exclude severe eczema and check for the presence of a vaccinia scar, respiratory, cardio-vascular and abdominal systems examination. An assessment of cervical and axillary lymph nodes will also be undertaken. The examination results and history of exposure to vaccinia will be recorded on the case record form. The general examination will be repeated at the final study visit.

#### **3.3 Genital infection screen**

The following will be collected in all participants

- serology for syphilis
- serology for markers of hepatitis B surface antigen or hepatitis C antibody

The following will be collected if indicated on account of risk and symptoms, according to trial specific clinical standardised operating procedures:

- urethral, vaginal, cervical and rectal specimens as appropriate for *Neisseria gonorrhoea*
- collection of urine for *Chlamydia trachomatis*
- vaginal swab for *Trichomonas vaginalis*

#### **3.4 Pre-HIV test screen and counselling**

Study personnel will assess volunteers for past and current risk of HIV infection using the screening proforma and counsel them prior to collecting blood for a HIV test. The counselling process will ensure that volunteers have sufficient knowledge about HIV infection to understand what the test is for, the implications of a positive, negative and equivocal result and the standard of care available for HIV infection locally. They will also be informed how and when they will receive the result, according to the local policy in each clinical centre.

#### **3.5 Safe sex counselling and condom provision**

Participants will be counselled by study personnel about the importance of condoms at screening and reminded on the day of each immunisation, or in the case of the third immunisation, at the preceding visit 2 weeks earlier. Hypo-allergenic condoms will be provided free of charge to participants throughout the trial.

#### **3.6 HIV related issues**

Please see section 6 for details of the procedures which may be required in the event of:

- 1) a request for a HIV test
- 2) HIV infection
- 3) Social discrimination as a result of post-vaccine response

#### **3.7 Discontinuation procedures (including withdrawal)**

Participants may withdraw at any time if they wish to do so, for any reason. The date of withdrawal and reason for doing so should be recorded in the appropriate case record form.

The clinical investigator may decide that it is not in the best interests of the participant to proceed to the next immunisation following an adverse event (see section 5.4.1 for recommendations). The discontinuation and reason should be recorded in the appropriate immunisation and reportable adverse event case record forms, which should be forwarded to

MRC CTU within the next 2 working days. Trial visits should carry on at least until resolution or stabilisation of the event, but ideally up to the last visit in the schedule, provided the participant is willing. The frequency of visits and laboratory investigations may be reduced on consultation with the Principal Investigator or Trial Management Group (see section 7).

### **3.8 Unblinding procedure**

This is an open trial for clinical investigators and participants.

## **4 Assessments**

### **4.1 Safety assessments**

#### **4.1.1 Local adverse events**

Pain in the muscle injected will be graded by the participant according to the criteria in appendix 4 as mild (1) moderate (2), severe (3) or extreme (4) and recorded in the appropriate case record form or once the participant has left clinic, in the diary card.

Redness will be recorded as the maximum diameter and expressed as a proportion of the arm or thigh circumference and graded on this criteria and the presence of symptoms according to appendix 4. Arm circumference will be measured at screening at the point one third of the way down from the acromio-clavicular joint towards the elbow joint of the non-dominant arm, and thigh circumference half way between the iliac promontory and the patella. Participants will be asked to record the maximum diameter in the diary card, as well as the presence of any itching or other discomfort and any medication taken for relief of symptoms.

Blistering (vesiculation) or ulceration will be graded according to size, depth, time to healing and character of blisters (blood-filled).

The presence of induration (hardened swelling) following intramuscular injection will be considered grade 3 if considered by the clinician to have arisen from a pathological process within the muscle. Induration considered in the judgement of the clinician to result from product leaking into the intradermal or subcutaneous layers will be graded according to the intradermal parameters in the toxicity table (Appendix 4). Soft swelling local to the injection site is not considered induration and should be graded according to the soft swelling parameters in the toxicity table (Appendix 4).

Clinical staff will complete the case record form following each immunisation. Completed case record forms and the diary cards will be sent to the data coordination centres to be recorded on the database. In the event that there are two observations on the same day, those confirmed at a visit will take precedence over diary card observations in the analysis.

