#### **4.1.2 Systemic adverse events**

Temperature will be measured by the oral route prior to immunisation and one hour later by study personnel, and graded according to appendix 4. Participants will be given digital thermometers to record their temperature in the diary card on the evening of immunisation, and daily thereafter for 7 days, and if still raised, they will be advised to continue to monitor their temperature daily until it returns to normal. The temperature observed by the clinical team will be recorded on the case record forms for visits.

Chills, headache, nausea, vomiting, malaise and myalgia will be graded by the participants according to appendix 4, recorded in the diary card on the evening following immunisation and daily for 7 days, or until resolution of symptoms whichever is longer. On days where a visit coincides with the diary card, the clinical staff will collect the information directly and record it on the case record form, and this will take precedence over diary card entries in the analysis.

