| Vomiting                        | Less than 4 x a day or lasting less than 1 week                        | At least 4 x day or lasting 1 week or more                               | Unable to keep any food or fluids down                         | Hospitalisation     |

- Complete at approximately the same time every day ONLY on days that you are NOT going to clinic
- Fill in temperature and record the grade of other general reactions (use the table above as a guide)
- Add any comments regarding other symptoms
- Record any medication taken including over the counter medicines and anything taken to relieve local reactions
- Record the grade, or size in cm, of local reactions overleaf
- Please contact a member of the trials staff as soon as possible if you experience any symptoms of grade 3 or 4
- When the diary card is complete, please return it to a member of trials staff at your next visit

|                                                               | 12 hrs      | Day 1       | Day 2       | Day 3       | Day 4       | Day 5       | Day 6       | Day 7       |
|---------------------------------------------------------------|-------------|-------------|-------------|-------------|-------------|-------------|-------------|-------------|
| General Symptoms                                       |             |             |             |             |             |             |             |             |
| Date                                                   |             |             |             |             |             |             |             |             |
| Temperature °C                                         |             |             |             |             |             |             |             |             |
| Chills/rigors                                          |             |             |             |             |             |             |             |             |
| Malaise/ tiredness                                     |             |             |             |             |             |             |             |             |
| General muscle aches                                   |             |             |             |             |             |             |             |             |

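### As written, the visit-over-diary rule lets a record made within an hour of injection displace a worse same-evening grade, and the diary card's own instruction may stop that evening entry being made

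*Protocol*

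**What the plan says.** **The precedence rule.** Protocol section 4.1.1 (local events) states that for "two observations on the same day, those confirmed at a visit will take precedence over diary card observations in the analysis". Section 4.1.2 (systemic events) says that when a visit coincides with a diary day, staff collect the information directly, and "this will take precedence over diary card entries in the analysis". Neither sentence excepts the day of immunisation.

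**What is recorded on that day.** Under section 2.3.1 the injection site is inspected at ten minutes. Then "participants will be closely observed for one hour after each immunisation, at which point vital signs" are recorded on the case record form, "as will any local or systemic reaction". Section 4.1.2 adds a staff temperature reading at one hour. It also has participants "record their temperature in the diary card on the evening of immunisation, and daily thereafter for 7 days", and asks for chills, headache, nausea, vomiting, malaise and myalgia to be entered that evening. Section 4.1.1 sends pain to the diary after the participant leaves the clinic. The card in Appendix 5 has eight columns for general and for local symptoms: 12 hrs, then Days 1 to 7.

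**The card's instruction.** Appendix 5 tells participants: "Complete at approximately the same time every day ONLY on days that you are NOT going to clinic".

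**Where the data go.** Solicited local and systemic events of grade 3 or above are primary safety parameters (section 1.5.1). They are compared between groups as proportions with Fisher's exact test (section 8.2). The secondary safety tables in section 8.3.2 use maximum grade.

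**The concern.** A precedence rule is harmless when the two records describe the same reaction at about the same time. On immunisation day they need not. The clinic record is closed about an hour after injection, and the diary entry is made hours later. Several grade 3 definitions in Appendix 4 depend on things that take time to happen, such as repeated analgesia for pain or headache, or a day in bed for malaise. A check at one hour can rarely meet them.

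The card instruction raises a separate problem of data collection. A participant who follows it leaves the first evening blank, and no later analysis rule can restore an entry that was not made.

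At stake is a primary safety endpoint. A reaction that reaches grade 3 on the first evening and has eased by the next day's entry could be graded from the one-hour check alone.

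**Working it through.** The protocol states no figure on this point, so the check is mainly a reading of the text, with one illustration.

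**1. Do the two records fall on the same day?** Every immunisation takes place at the clinic, with observation to one hour (section 2.3.1). The diary entry is due that evening (section 4.1.2). They do, and the literal rule applies.

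**2. Direction of any effect.** Let *c* be the clinic grade and *e* the evening diary grade on immunisation day.

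- Literal rule: grade analysed = *c*.
- Worst-of-day rule: grade analysed = max(*c*, *e*), which is at least *c*.

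Dropping *e* can lower the day's grade and can never raise it. Any bias in the proportion with grade 3 or above is downward.

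**3. How the two mechanisms relate.** For a given evening they are alternatives. If the card instruction is obeyed, there is no *e* to displace. If the 12 hrs column is filled in, the precedence rule can set *e* aside. Their losses must not be added together, but each needs its own correction.

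**4. Extent of exposure.** Four immunisations per participant (section II) and 140 participants give 4 × 140 = 560 immunisation-evening entries, one of the eight columns on each card. This counts diary entries exposed to the problem, not severe events lost.

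**5. Illustration of size.** Let *p* be the true proportion with a grade 3 or above reaction. Let *f* be the share of those participants whose only grade 3 or above record is the first-evening diary entry and who are not picked up by another route. The literal rule then yields *p*(1 − *f*). The protocol gives neither *p* nor *f*, so both are assumed here. With 70 per group (section 8.1), *p* = 5% and 15%, and the same *f* in both groups:

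- Expected participants with grade 3 or above: 70 × 0.05 + 70 × 0.15 = 3.5 + 10.5 = 14.
- Expected number lost: 14 × *f*.
- Power is that of the exact two-sided Fisher test at the 5% level, by enumeration.

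| *f* (assumed) | Lost of 14 | Fisher power |
|---|---|---|
| 0 | 0 | 41% |
| 0.10 | 1.4 | 35% |
| 0.25 | 3.5 | 27% |
| 0.50 | 7.0 | 13% |

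With 5% in both groups, the expected total is 7, and *f* = 0.25 loses 7 × 0.25 = 1.75. If *f* = 0, nothing is lost. The table shows how the result depends on *f*; it does not estimate *f*.

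**The case against.** The best defence is that the precedence sentence in section 4.1.1 concerns observations confirmed at a visit, which can naturally mean two records of one reaction. Section 4.1.1 treats the day in sequence (clinic form first, then diary), section 4.1.2 deliberately schedules both a one-hour and an evening temperature, and the card gives 12 hrs its own column. A reading that makes a planned entry useless is arguably not the intended one. This stands as a reason for caution about intent. It does not remove the ambiguity, because neither sentence says so, and it does not resolve the card's instruction.

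Other routes could also recover events. Participants are asked to contact staff about any grade 3 or 4 symptom (Appendix 5). The team keeps in contact until solicited events resolve (section 2.3.2). Adverse events are assessed at later visits (section 2.6), and diary entries on non-visit days are untouched. Some grade 3 criteria cannot be met in a single evening: minimal intake for three days or more for nausea, or leakage induration lasting more than six days. Peak temperature, vomiting and myalgia are among the few that could be confined to one. All of this stands and limits the size. No passage, however, says that a called-in grade overrides the visit record.

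A reader might go on to infer three stronger things that the protocol does not support:

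- **That the loss differs between arms**, because group 2 has two NYVAC-C days and group 1 has one. Both groups have four immunisation days, and nothing shows that severe reactions confined to the evening differ by product.
- **That the same loss occurs at follow-up visits.** The visits after DNA-C fall nominally at day 7, the end of the diary period, and those after NYVAC-C two weeks after injection. Staff collect the grade directly at these visits.
- **That a substantial known share of severe reactions is lost.** The protocol gives no rate and no share.

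**Conclusion.** The point holds as a defect of wording and data collection. The precedence rule as written covers immunisation day and lets an observation from the first hour outrank a later, worse one. The card instruction contradicts section 4.1.2 and the card's own 12 hrs column; that contradiction needs no assumption.

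It would be tempting to conclude that the primary safety endpoint does under-count severe reactions. The protocol does not establish this. An event is lost only if it reaches grade 3 on the first evening, is below grade 3 by the next diary entry, and is missed by the call-in, continued contact and later visits. What can be said is that any bias is downward and that its size cannot be determined. It may be small or zero, and the tabulated losses rest wholly on assumed rates.

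This should be fixed, with medium confidence. It goes beyond detail that could be left to an analysis plan, because the card determines whether the data exist at all.

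**What to change.** 1. In sections 4.1.1 and 4.1.2, replace the precedence sentences with a rule that the grade analysed for a day is the maximum of the clinic and diary grades for that day. This agrees with the maximum-grade tables in section 8.3.2. Alternatively, keep visit precedence but limit it to observations of the same reaction at the same time.
2. In Appendix 5, remove the restriction to non-clinic days as far as it affects immunisation days, and tell participants to complete the 12 hrs column on each immunisation evening.

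Both changes are needed: the first cannot help if the entry is never made, and the second achieves little if the entry can be set aside.

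The cost is a change to two protocol sentences, matching analysis wording and a revised card. The downside is that a few diary grades not confirmed at a visit will count, so reported rates may rise slightly.
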